### Criteria for discontinuing or modifying allocated interventions {11b}

Participants have the right to withdraw from the study at any time and for any reason, without facing any negative consequences. They will be assured that their decision to discontinue participation will not affect the quality of their clinical care in any way.

Additionally, participants may request to stop the intervention at any stage of the study. If a participant experiences emotional distress, health-related complications, or any other condition that makes continuation inappropriate, the intervention may be paused or terminated based on the researcher’s clinical judgment. All reasons for discontinuation or modification will be recorded and documented accordingly.

### Strategies to improve adherence to interventions {11c}

To improve adherence to the intervention protocol, participants will receive weekly reminders via text messages to attend the scheduled sessions. Additionally, regular follow-up calls will be made by the researcher to assess participant progress and address any concerns. Adherence will also be monitored by tracking attendance at intervention sessions and any required reports or questionnaires. Any missed sessions will be rescheduled, and participants will be encouraged to communicate any barriers to adherence.

*Relevant concomitant care permitted or prohibited during the trial {11d*
**}.**

During the study period, participants are prohibited from participating in additional structured educational sessions related to Parkinson’s disease (e.g., nutrition or lifestyle workshops offered by organizations such as the Isfahan Parkinson’s Charity Association) to prevent confounding effects on the study outcomes. This restriction does not apply to routine medical care, including prescribed medications, physiotherapy, or other standard treatments for Parkinson’s disease, which participants are permitted to continue under the supervision of their healthcare providers to ensure their welfare is maintained.

### Provisions for post-trial care {30}

As the intervention is educational and does not involve any pharmaceutical treatments or interventions with side effects, there are no specific post-trial care requirements. However, participants will be followed up for a period of 3 months after the trial to assess any long-term impact of the intervention on their knowledge and self-management of Parkinson’s disease. If any participant experiences any issues related to the study, they will be referred to appropriate healthcare professionals for further support.

Since the intervention poses no direct risk, no compensation is anticipated for harm from trial participation. However, any concerns raised by participants during the post-trial follow-up will be addressed promptly.

### Outcomes {12}

The primary outcome is quality of life, measured using the PDQ-8, at 1 month post-intervention to assess sustained effects. Secondary outcomes include fatigue (PFS-16) and self-efficacy (GSE-17), assessed at baseline, immediately post-intervention, and 1 month post-intervention. Data collection will be coordinated via telephone, and participants will be asked to visit the Isfahan Parkinson’s Charity Association to complete the questionnaires. If a participant is unable to attend, the researcher will complete the questionnaire at the participant’s residence.

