### Who will take informed consent? {26a}

Before participation, all eligible patients will receive both oral and written information about the study, including its objectives, procedures, potential risks and benefits, and their rights as participants. Adequate time will be given for questions and consideration.

Informed written consent will be obtained by the researcher, [name] [name], a master's student in nursing and the person responsible for conducting the intervention.

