Ninth stage: control phase	• Learners are expected to have sufficient knowledge of previous sessions and actively express their understanding during the review of past topics • Learners should articulate any questions or challenges they face and implement the solutions provided by the researcher • Learners should actively describe the health behaviors they have adopted since the completion of the sensitization sessions	• Continuation of continuous Care Consultations to Sustain Health Behaviors Based on Patients’ Needs and Challenges • Encouraging Patients to Maintain Healthy Behaviors	• Phone Call and Q&A	Researcher	30 to 45 min
Tenth stage: evaluation phase	• Completion of Questionnaires by Participants • Learners should express any new or unresolved issues and listen to the solutions provided by the researcher or the experiences of other participants regarding the existing problem	• Review of the Care Process, Evaluation of Key Indicators through Recompletion of Questionnaires, and Monitoring and Controlling Patient Behavior and the Impact of Provided Training • Assessment of Unresolved Issues or the Emergence of New Problems	• Lecture • Q&A • Group Discussion	Researcher	30 to 45 min

In the monitoring phase, follow-up care counseling continues to reinforce the maintenance of healthy behaviors. This phase is carried out over 4 weeks through four telephone calls (one call per week) with the patient and, if necessary, with their caregiver. The content of these calls is tailored to the patient's specific problems and needs.

A key component of this phase is encouraging the patient to sustain healthy behaviors and referring them to a specialist if required. Additionally, a contact number will be provided to patients and their caregivers, allowing them to reach out with any questions and receive necessary guidance [40].

The evaluation phase, which is the final step of the intervention, involves assessing the care process, evaluating key indicators through the reassessment of questionnaires, and monitoring the patient’s behavior to determine the impact of the provided education. Additionally, any unresolved issues or newly emerging problems will be examined [40].

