## Assignment of interventions: blinding

### Who will be blinded {17a}

Due to the nature of the intervention, this study will not be blinded. The researcher administering the intervention and the patients will be aware of their group assignments, as participation in the intervention requires awareness of the assigned group. Therefore, concealment of allocation is not feasible, and the study is designed as an open-label trial.

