### Data management {19}

Data will be collected using paper-based questionnaires completed by participants. Responses will be entered into a password-protected laptop by the researcher. Each participant will be assigned a unique code, and no names or personal identifiers will be stored. As the data consist of numerical values only, no advanced security measures are applied. Data quality will be ensured through careful data entry and periodic checks for completeness and consistency.

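### At the immediate post-intervention assessment the intervention arm answers its questionnaires inside a researcher-led session that controls do not have, and the protocol contradicts itself on who fills in the form at home visits

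*Protocol article*

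**What the plan says.** **Who delivers and who knows.** Section {26a} describes the researcher who takes consent as "the person responsible for conducting the intervention". Table 1 names the researcher as presenter of all ten stages. Section {17a} states: "The researcher administering the intervention and the patients will be aware of their group assignments".

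**Immediate assessment, intervention arm.** In Table 1, under {11a}, the tenth stage lists "Completion of Questionnaires by Participants" among its objectives and "Evaluation of Key Indicators through Recompletion of Questionnaires" in its content. The teaching method is "Lecture • Q&A • Group Discussion". The text after the table treats this evaluation phase as the last step of the intervention.

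**Control arm.** According to {11a}, controls receive no intervention and stay on routine care. They therefore have no tenth session.

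**General collection rule.** Section {12} says: "Data collection will be coordinated via telephone, and participants will be asked to visit" the Association. For those who cannot come it says: "If a participant is unable to attend, the researcher will complete the questionnaire" at the participant's home. Neither rule is split by arm or by time point.

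**Data management.** Section {19} says: "Data will be collected using paper-based questionnaires completed by participants". The researcher then enters the responses.

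**Use of the data.** The primary outcome is PDQ-8 at 1 month. Fatigue and self-efficacy are assessed at baseline, immediately after and at 1 month ({12}). Section {20a} analyses all three outcomes over all three time points by repeated measures ANCOVA.

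**The concern.** PDQ-8, PFS-16 and GSE-17 are all subjective self-reports. Intervention patients rate themselves at the end of the programme as one item in a session run by the person who taught them, among fellow participants, with discussion of how things have gone. Controls rate themselves with none of this around them. A tendency to give the teacher a favourable answer would then act in one arm only, and the data could not separate it from a treatment effect. Baseline adjustment does not help, because baseline is taken before randomisation and the difference in setting arises afterwards.

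The home-visit wording raises a second, distinct risk. Read literally, it lets an unblinded person with an interest in the result fill in a subjective outcome, including the primary PDQ-8 at 1 month.

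**Working it through.** **1. The measurement setting at each time point, as documented**

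| Time point | Intervention arm | Control arm | Documented difference by arm? |
|---|---|---|---|
| Baseline | Own session of 30–45 min, before randomisation ({11a}) | Same | No |
| Immediately after | Within session ten: researcher-led, lecture, Q&A, group discussion (Table 1) | Visit or home ({12}); no session ({11a}) | Yes |
| 1 month (primary PDQ-8) | Visit or home ({12}) | Visit or home ({12}) | No |

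Session ten is allotted 30–45 min for questionnaires and discussion together. The baseline forms alone, which also include the demographic form, have a 30–45 min session of their own. The order of events within session ten is not given.

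**2. Who fills in the form**

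Section {19} and Table 1 say the participant. Section {12}, for home visits, says the researcher. Both cannot hold as written.

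**3. The plan's own sample size**

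From {14}: SD 6, difference 4, 80% power, z values 0.84 and 1.96.

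n = 2 × 6² × (0.84 + 1.96)² / 4² = 35.28, rounded up to 36 per arm, 72 in total. Allowing for 10% dropout, 72 / 0.9 = 80. The stated figures reproduce.

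**4. Illustration of scale**

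Assumptions: no true effect; a reporting shift b between the arms, whose size is not in the documents; SD 6 taken as applying to PDQ-8 (8 items scored 0–4, so 0–32); an unadjusted two-sided z-test at 5% at one affected time point.

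- SE = 6 × √(2/36) = 1.414
- P(reject) = Φ(b/SE − 1.96) + Φ(−b/SE − 1.96)

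| Assumed b (points) | b as share of the 4-point target | b/SE | False-positive rate |
|---|---|---|---|
| 0 | 0% | 0 | 5.0% |
| 0.5 | 12.5% | 0.354 | 6.4% |
| 1 | 25% | 0.707 | 10.9% |
| 2 | 50% | 1.414 | 29.3% |

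With 40 per arm the last three rates become 6.6%, 11.6% and 32.0%.

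**5. How far a shift at the immediate assessment carries**

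If the shift is present only at the immediate assessment, a group difference averaged equally over the two post-baseline assessments moves by b/2. Averaged over all three time points it moves by b/3. A comparison confined to 1 month does not move through this route. The table in step 4 therefore applies to a comparison at the affected time point, not to the whole analysis.

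**The case against.** Four objections have weight.

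- **The primary time point.** A reader might infer that the primary result is measured differently in the two arms. The documents do not support this. Session ten falls at the end of the intervention, and for 1 month {12} gives both arms one procedure. This limit stands and is built into the point.
- **The home-visit rule covers both arms.** A reader might take it as a further difference by arm. It is not one as written. It is a risk from an unblinded collector. Social pressure might still be unequal, because the researcher has taught one arm and not the other, but that is inference.
- **The verb is ambiguous.** The home-visit wording may mean only that the researcher sees that the form gets completed. Section {19}, Table 1 and the eligibility criteria on literacy and vision ({10}) all point to self-completion. Proxy completion is therefore not established. The contradiction in wording remains.
- **Table 1 does not say how the forms are filled in.** It does not state that they are answered after the discussion or in the presenter's view, and private completion on arrival would fit the text. A condensed article may leave that detail to the full protocol. What the article does state is that completion is part of a session only one arm attends.

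It can also be said that blinding is impossible here. That is true of patients and interventionist, and {17a} discloses it. It does not require outcomes to be collected inside a teaching session.

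**Conclusion.** The concern holds in a limited form. The protocol builds a difference in measurement setting between the arms into the immediate post-intervention assessment. This affects one of the two post-baseline time points for both secondary outcomes, and one of the three time points in the ANCOVA for every outcome. It does not reach the primary PDQ-8 at 1 month when that is compared on its own.

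Separately, {12} and {19} disagree on who fills in the form at home visits, and that disagreement does extend to the primary time point, in both arms.

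The size of any bias is unknown. Assumed shifts of 0.5 to 2 points give false-positive rates of about 6.4% to 29.3% at an affected time point. This shows sensitivity and does not predict a bias. The illustration covers PDQ-8 only, since the protocol gives no SD for PFS-16 or GSE-17. The weakness is avoidable and cheap to correct, and it does not invalidate the design.

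**What to change.** - **Same procedure in both arms.** Participants fill in the forms themselves, privately, with identical written instructions, and seal them in a coded envelope.
- **Separate measurement from teaching.** In the intervention arm this is done before session ten starts. Take questionnaire completion out of the session's activities in Table 1.
- **Reconcile {12} with {19}.** Reword {12} so that at home visits the participant self-completes and the researcher only delivers and collects the form. Before the envelope is sealed, the researcher checks only that no item is blank. This check matters because {20c} excludes participants with incomplete data.
- **Record help.** Note every form completed with assistance, and run a sensitivity analysis without those forms.

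The cost is wording, instruction sheets and envelopes, with no extra staff and no change in sample size. There are downsides. A few patients may need help with writing, slightly more forms may be incomplete, and the check for blanks gives the researcher a brief view of the answers. Expectation bias from the open-label design remains, and so does data entry by the researcher.

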### Participant timeline {13}

#### Sample size {14}

To determine the sample size, assuming a normal distribution of quality-of-life data, the following formula will be used.$$n= \frac{2 \times {\sigma }^{2}{ \times ({Z}_{1-\beta }+ {Z}_{1-\alpha /2})}^{2}}{{({\mu }_{1}-{\mu }_{2} )}^{2}}$$

The standard deviation in the study by Moghtaderi et al. was reported to be approximately 6 [41]. Therefore, with a power of 80% (1 − β = 80%) and assuming a confidence level of *α* = 0.05, the required sample size for each group to detect a difference of 4 units (μ₁ − μ₂ = 4) is:$$n=\frac{2 \times {6}^{2} \times {(0.84+ 1.96)}^{2}}{{(4)}^{2}}=35.28\approx 36$$

The required sample size for each group will be 36 participants, resulting in a total of 72 samples. Considering a 10% dropout rate, a total of 80 participants will be required for the study.

### Recruitment {15} (Fig. 1)

A total of 80 patients diagnosed with PD who meet the inclusion criteria will be recruited from the Isfahan Parkinson Charity Association. After obtaining official approval from the School of Nursing and Midwifery, Isfahan University of Medical Sciences, and presenting it to the association’s authorities, the researcher will enter the study environment and screen participants based on inclusion criteria with confirmation from a neurologist specializing in movement disorders. The estimated duration for the recruitment process is approximately 2 months.

**Fig. 1 Fig1:**
[figure not shown]
Consort Diagram

## Assignment of interventions: allocation

### Sequence generation {16a}

From all registered patients, 80 eligible participants will be selected using a convenience sampling method. They will be randomly assigned into two groups: 40 in the intervention group and 40 in the control group.

Participants will be allocated using block randomization. The intervention group will be labeled “A” and the control group “B.” The six possible block arrangements (AABB, ABBA, ABAB, BAAB, BABA, BBAA) will be written on separate cards.

A number between 1 and 6 will be randomly selected (using a random number table). For instance, if block 2 (ABBA) is chosen, the first patient will be assigned to the intervention group, the next two to the control group, and the fourth to the intervention group. This process will continue until the required sample size is reached.

### Concealment mechanism {16b}

The allocation sequence will be concealed until the interventions are assigned. Block randomization will be used to assign participants to either the intervention group (Group A) or the control group (Group B).

To prevent any bias, the block sequences will be written on separate cards or in sealed envelopes. These envelopes will be kept secure and will not be accessible to the researchers who are enrolling participants. This ensures that the allocation sequence remains concealed until the moment of random assignment.

### Implementation {16c}

The random allocation sequence will be generated using a random number table.

[name], the principal investigator, will be responsible for enrolling participants, obtaining informed consent, and assigning them to the intervention or control groups based on the pre-generated block randomization sequence.

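### Three sections of the protocol contradict each other on allocation concealment, and the procedure they describe cannot deliver the concealment that {16b} promises

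*Protocol article*

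**What the plan says.** All references are to the protocol article.

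- **Sequence generation {16a}**: 80 eligible patients are taken by convenience sampling and allocated 40:40. The six orderings of two As and two Bs are each put on a card, and a random number from 1 to 6 picks the card. The worked example shows that one draw settles four consecutive patients: "if block 2 (ABBA) is chosen, the first patient will be assigned to the intervention group, the next two to the control group". The same card also settles patient four.
- **Concealment mechanism {16b}**: "The allocation sequence will be concealed until the interventions are assigned". The container is described so: "the block sequences will be written on separate cards or in sealed envelopes". On access: "These envelopes will be kept secure and will not be accessible to the researchers who are enrolling participants".
- **Implementation {16c}**: the principal investigator "will be responsible for enrolling participants, obtaining informed consent, and assigning them to the intervention or control groups", and does so "based on the pre-generated block randomization sequence".
- **Who will be blinded {17a}**: because patients and the researcher will know the group, "concealment of allocation is not feasible, and the study is designed as an open-label trial".
- **Intervention description {11a}**: written consent and the baseline questionnaires come first, and random assignment follows.

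**The concern.** Allocation concealment means that whoever decides on a patient's entry cannot know that patient's allocation beforehand. It is separate from blinding and can be achieved in an open-label trial. Here one section promises it, the next gives enrolment and assignment to the same person, and a third says it cannot be done. Site staff could follow any of the three and claim to be following the protocol.

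The stake is selection bias. With convenience sampling the recruiter has latitude over whom to approach and when, and several eligibility items rest on judgement, such as willingness and the absence of illness that would prevent taking part. A recruiter who knows or can guess the next allocation could, deliberately or not, bring more motivated or milder patients into the intervention arm. Baseline scores and covariate adjustment would correct this only in part, because motivation is not measured.

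**Working it through.** **1. The sections side by side**

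| Question | {16b} | {16c} | {17a} |
|---|---|---|---|
| Is allocation concealed until assignment? | Yes | Not addressed | Not feasible |
| Can the enroller reach the allocations? | No | The enroller assigns from the sequence | Not addressed |
| Is there an independent holder? | None named | None named | None named |

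{16b} and {16c} conflict on access: a person who assigns from the sequence must hold it or be handed its contents. {16b} and {17a} conflict outright on concealment. The reason given in {17a}, that people know their group, describes lack of blinding after assignment. It does not show that concealment before assignment is impossible.

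**2. The plan's own numbers**

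Blocks of 4 ({16a}) and 80 patients give 80 / 4 = 20 blocks, each with 2 A and 2 B, so 40:40. This agrees with the stated arm sizes.

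**3. If the assigner sees the card when a block opens**

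This assumes patients are enrolled one at a time. The first patient of a block is unknown until the card is drawn, and patients 2, 3 and 4 are then known. Known in advance: 3 per block × 20 blocks = 60 of 80 (75%).

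**4. If the cards are never seen**

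This assumes only that the recruiter knows the block size is 4 and, the trial being open label, knows past allocations. The six orderings are equally likely.

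| Position in block | Probability that the allocation is certain | Probability that the best guess is right |
|---|---|---|
| 1 | 0 | 1/2 |
| 2 | 0 | 2/3 |
| 3 | 1/3 (first two alike) | 1/3 × 1 + 2/3 × 1/2 = 2/3 |
| 4 | 1 | 1 |
| Sum per block | 4/3 | 17/6 |

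- Certain in advance: (4/3) / 4 = 8/24 = 33.3%, or 20 × 4/3 ≈ 27 of 80.
- Best guess right: (17/6) / 4 = 17/24 = 70.8%, or 20 × 17/6 ≈ 57 of 80, against 50% (40 of 80) by chance.

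**5. Arm sizes under mixed blocks of 4 and 6**

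All block sizes are even, so at patient 80 an unfinished last block has 2 or 4 patients filled. The largest imbalance is 2:0 (2 filled) or 3:1 (4 filled of a block of 6), a difference of 2. The worst split is therefore 41:39.

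**The case against.** The strongest reply is that {16b} commits in plain terms to concealment. A reader might infer from {16c} and {17a} that allocation is simply not concealed, or that the investigator will hold the list and know all 80 allocations. The documents do not support that as fact: {16b} states the opposite intention, {16c} does not say who physically keeps the list, and {17a} sits under a blinding heading and is most likely a misuse of the term. What stands is the contradiction, and the absence of any described step that would make the promise good.

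Second, 60 of 80 is a scenario. No section says that the assigner sees the full card or that patients enter strictly one by one. {16a} can also be read as assembling the patients first and then randomising them. In that case foreknowledge would affect which patient takes which place in the order, not who is enrolled. This objection stands, so the figure is a worst case. The worked example in {16a} does make block-level disclosure a natural reading.

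Third, {11a} already places consent and baseline assessment before assignment. That is correct and protects the baseline scores. It does not stop foreknowledge from influencing whom the recruiter approaches next.

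Fourth, the 33% and 71% figures would apply to any open-label trial with a known fixed block of 4, even with ideal envelopes. That also stands. They argue for varying the block size and do not prove the contradiction.

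Two further inferences should be resisted. It is tempting to say that patients with a supportive relative could be steered to the intervention, but the eligibility criteria require a family member for every participant. It is also tempting to tie this to the self-reported outcomes, but measurement bias from open-label self-report is a separate problem that concealment would not change.

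**Conclusion.** {16b}, {16c} and {17a} cannot all be followed, and the procedure as described does not secure the concealment that {16b} states. This rests on the text alone and needs no assumption.

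The extent of foreknowledge depends on conduct: 60 of 80 allocations in the worst case, and about 27 of 80 certain with a best guess right for about 57 of 80 if cards stay unseen but the block size and past allocations are known. The size of any resulting bias in the treatment effect cannot be calculated from the documents. The point should be settled before recruitment, because selection on unmeasured characteristics cannot be repaired in the analysis.

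**What to change.** 1. Have a member of the existing advisory committee, who neither enrols nor treats, generate and hold the list. Name this role in {16b} and {16c}.
2. Replace block cards with one sequentially numbered, opaque, sealed envelope per patient (80 in all), opened only after the consent and baseline assessment that {11a} already puts first.
3. In {16c}, remove assignment from the enroller's duties.
4. In {17a}, state that blinding, not allocation concealment, is not feasible.
5. Secondary: mix block sizes at random (for example 4 and 6) and do not disclose them to the recruiter.

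The cost is some rewording, 80 envelopes and a short task for someone already attached to the trial. Step 5 may give a 41:39 split. The sample size is unaffected.

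The trial status section expected recruitment from about June 15 to July 15, 2025. If it has started, the sponsor should document how allocation was actually done, including who held the sequence and when cards or envelopes were opened, and correct the three sections to match.
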